**Figure 1. f1:**
[figure not shown]
Consort flow diagram.

The play therapy manual has been developed by the Principal Investigator with the activities specified as per the domains of child development including physical development, language and communication skills, socio-emotional development, and cognitive development. A couple of parents and children were involved and their inputs were included in the development and piloting of the Play Therapy Manual. The Play Activity manual
^
24
^ is available in the extended data.

The Principal Investigator will train the team of Research Assistants on the intervention package. The trained and certified Research Assistants will deliver the intervention in hospital setting and then at home visits as per the schedule drafted by Principal Investigator.

### Duration of the interventions

1.All the children who fall in the age range of six months to five years (60 months) old will receive the intervention (along with their parents) every day (minimum three days) during their hospital stay for one hour per day.2.The children will receive monthly follow-up sessions through home visits (or through social media group meetings if needed) for one hour every week till 12 months from enrolment in the program.3.Activities described in the Play Therapy Manual will be followed for the follow-up sessions.

### Criteria for group sessions at the hospital

The hands of parents and their children will be washed before the activities start to avoid infectious contamination. Children will be divided into two groups as below:
1.Six months to 30 months old2.31 months to 60 months.

The intervention delivery details are as below:

On first day of hospitalization, parents and children will be interacted at Paediatrics ward. Randomization will be done and the parents in intervention arm will be sensitized about Play Therapy Programme. Written informed consents of parents will be taken from those who consent for participation and will be enrolled in the programme and e-learning platform/Whatsapp group.

On second day of hospitalization, a session will be conducted at designated play area in hospital. The session will emphasize on importance of early child development, its implications; diet, nutrition and healthcare of children. This session will be followed by play interaction session on cognitive and language development.

On third day of hospitalization, a play session on motor developmental activities will be conducted. This will be followed by session on socioemotional development and activities to promote it. Relevant Documents and reading materials in local language will be shared with parents during these sessions. The enrolled children will participate in play sessions and activities till the child is hospitalized.

After discharge from the hospital, parents and children will be contacted through monthly home visits personally and if needed, through online mode (Whatapp video call/Google classroom) at monthly intervals. The home visits will be scheduled for the assessment of Home Environment and Parent-Child Interactions. The monthly sessions will be continued till one year from the date of enrolment of child in the programme. Appropriate medical and nursing care will be provided during the hospital stay. If needed, referral services will be provided during follow-up at-home visits. If Children and parents insist on discontinuing play therapy, the sessions will be discontinued for those children.

After one-year of enrollment, assessments of age-appropriate developmental milestones of children will be done either in the hospital ECD Centre or through personalized home visit to the enrolled family. Age-appropriate assessment tools will be used. Reports will be shared with parents, and follow-up instructions and meeting schedules will be shared.
Figure 2 shows the schedule of enrolment, interventions, and assessments.

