### Eligibility criteria

*Inclusion criteria:*
1.Children admitted to the Paediatric Ward of A.V.B.R.H. aged six months to 60 months.2.Children from villages within 25 Km periphery of A.V.B.R.H.3.Parents consenting to the participation of their child in the Play Therapy Programme.

*Exclusion criteria:*
1.Seriously sick, moribund children with life-threatening conditions.2.Children in Intensive Care treatment.

The Investigator will take written informed consent from the parents of the hospitalized children. The comparator (control) group will include children from the adjoining paediatric ward on another floor and admitted during the period when interventions will not be implemented. Children from this group will receive all required treatment and nursing care except the Play therapy sessions. This will help to avoid any contamination. Baseline assessments and socio-demographic information of these children will be collected at enrolment. Follow-up home visits will be done at monthly home visits. Assessments will be done at six months and 12 months from the date of enrolment. If successful, the children from control group will receive play therapy after the trial is over.

The children and their parents signing the informed consent will be enrolled in the study. All enrolled children hospitalized in A.V.B.R.H., scheduled to stay for a minimum of three days in the hospital, will be assigned a Unique ID. Children will be allocated to intervention or control groups using a block randomization process
^
22
^
^,^
^
23
^ with age groups as the blocking variable. Intervention group will receive the play therapy sessions along with the required treatment and nursing care during hospitalization stay. Sociodemographic profile and baseline assessments will be done. Play therapy sessions will be conducted at the dedicated play area in hospital. Also, these children from the intervention area will receive the play sessions at scheduled monthly home visits.
Figure 1 shows the anticipated Consort Flow Diagram of study participants.

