### Assignment of interventions: allocation

All participants consenting to participate in the study will be assigned the Unique ID. Sequence generation will be done using computer generated random numbers. Using a block randomization process
^
10
^
^,^
^
11
^ with age groups as the blocking variable, participants will be allocated either to intervention or control groups.

Sequentially numbered, opaque, sealed envelopes will be used for implementing the allocation sequence.

The Principal Investigator will generate the allocation sequence, trained assistants will enroll the participants, and assign participants to intervention and control groups. The Principal Investigator will train the Research Assistants for intervention, and assessors for baseline-endline assessments, supervise the data collection process and monitor the trial implementation process. We will ensure that all adults associated with the trial have the appropriate permissions and training and criminal records check to work with children. The outcome assessors and data analysts will be blinded.

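### The day-1 description puts randomisation and a one-arm talk before written consent, while three other sections put consent first; the order must be reconciled and what was done reported

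*Protocol article*

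**What the plan says.** The day-1 paragraph is in the protocol article under Criteria for group sessions at the hospital. After contact with the family on the ward it says: "Randomization will be done and the parents in intervention arm will be sensitized about Play Therapy Programme". The next sentence is: "Written informed consents of parents will be taken from those who consent for participation and will be enrolled in the programme". Read in order, the steps are contact, randomisation, sensitisation of one arm, consent, enrolment.

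Three other sections give the opposite order.

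- Eligibility criteria: "The children and their parents signing the informed consent will be enrolled in the study". A Unique ID follows, and then "Children will be allocated to intervention or control groups using a block randomization process".
- Recruitment: consenting participants receive the Unique ID and are then allocated within age group.
- Assignment of interventions: allocation: "All participants consenting to participate in the study will be assigned the Unique ID", and then, "with age groups as the blocking variable, participants will be allocated either to intervention or control groups".

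The allocation section also fixes the mechanism and the staff: "Sequentially numbered, opaque, sealed envelopes will be used for implementing the allocation sequence", and "trained assistants will enroll the participants, and assign participants to intervention and control groups". The text following Figure 2 says that control families get no intervention messages, so the day-1 talk goes to one arm only.

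**The concern.** Sealed envelopes protect entry to a trial only while they stay sealed until the family has agreed to join. If the envelope is opened first, the arm is known to the parents and to the assistant who seeks consent. That assistant also makes the assignment, so no separation of roles offsets the loss.

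One arm would by then have heard a talk on the value of the programme and the other would not. Parents might then accept or refuse at different rates, or for different reasons, in the two arms. Because enrolment follows consent in that paragraph, a family that refused after allocation would not be enrolled. The groups compared at one year would be those who agreed after learning their arm, which need not be the groups that randomisation formed. A larger sample does not remove a bias of this kind.

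**Working it through.** **Order of steps, side by side**

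| Section | Order as written |
|---|---|
| Criteria for group sessions at the hospital (day 1) | randomise; sensitise intervention parents; consent; enrol |
| Eligibility criteria | consent and enrol; Unique ID; allocate |
| Recruitment | consent; Unique ID; allocate |
| Assignment of interventions: allocation | consent; Unique ID; allocate by envelope |

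Both orders cannot hold for the same family. Nothing in the visible text reconciles them or says how a family randomised but not consenting would be counted. Figures 1 and 2 are not visible.

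**The plan's own figure.** The finding rests on no number in the plan. For context, with d = 0.5, SD = 1.69 and z-values 1.96 and 0.84 (Sample size), n = 2 × (1.96 + 0.84)² × 1.69² / 0.5² = 179.1, so 180 per arm. This reproduces the stated size, and the order of consent does not change it.

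**Illustration of the mechanism.** Let a share r of intervention families decline after learning their arm. Let decliners score k SD below accepters, and let control entry be unaffected. The mean of all randomised families is (1 − r) × accepter mean + r × decliner mean, so accepters lie r × k SD above it. The spurious difference in an unadjusted comparison of one-year scores is therefore r × k × 1.69 points. Its standard error with 180 per arm is 1.69 × √(2/180) = 0.178. The documents give neither r nor k, so every row is an assumption.

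| r | k (SD) | Spurious difference (points) | Share of the 0.5 target | Two-sided type I error at nominal 5% |
|---|---|---|---|---|
| 5% | 0.25 | 0.02 | 4% | 5.2% |
| 10% | 0.5 | 0.08 | 17% | 7.6% |
| 20% | 0.5 | 0.17 | 34% | 15.8% |
| 30% | 0.5 | 0.25 | 51% | 29.6% |

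The sign is not known either. If decliners score higher, or if refusals fall in the control arm instead, the bias reverses. If refusals are alike in both arms, it vanishes.

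**Effect of the planned analysis.** Statistical methods names a difference-in-difference analysis. If decliners differ from accepters by k₀ at baseline and k₁ at one year, the bias in that analysis is r × (k₁ − k₀) SD. A fixed gap (k₁ = k₀) cancels completely. Bias remains only if decliners would have changed differently over the year, and the documents give nothing from which to estimate that.

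**The case against.** The strongest reply is that the sections that govern entry agree with each other. The day-1 paragraph is a short narrative of how the intervention is delivered, with no connecting word to fix the sequence of its sentences. Its consent sentence goes on to mention an e-learning platform and a messaging group, which only intervention families could join. It may therefore describe sign-up to the programme and not entry to the trial. The schedule (Figure 2) and the flow diagram (Figure 1) cannot be seen and might settle the order or count refusals.

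Most of this stands as a reason for caution. It does not remove the contradiction. The paragraph speaks of written informed consent and of enrolment, and the third inclusion criterion words trial consent as consent to the play therapy programme. The sign-up reading is possible but not secure.

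Three stronger readings are tempting, and the documents do not support them.

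- A reader might infer that consent was in fact taken after allocation and that the comparison is not randomised. The text shows only that the protocol states both orders.
- A reader might infer that baseline was measured after sensitisation, because Eligibility criteria mentions baseline assessment after allocation. That rests on sentence order alone. By the same logic baseline would follow the play sessions. The only timing stated there is at enrolment, for controls.
- A reader might take a percentage of the planned effect as the size of the bias. Any such figure comes from assumed refusal rates and gaps, and it ignores what the difference-in-difference analysis removes.

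**Conclusion.** The protocol contradicts itself on whether consent precedes allocation, and the passages must be reconciled. If the three entry sections describe what was done, the fault is one badly worded paragraph. If the day-1 order was followed, envelope concealment did not protect enrolment, and knowledge of the arm could have influenced who entered. It cannot be said to have decided it.

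The size of any resulting bias cannot be derived from the documents. The tabulated values show only that it could range from negligible to about half the 0.5-point target in an unadjusted comparison, under assumed one-sided refusal of 5 to 30% and a gap of 0.25 to 0.5 SD. In a difference-in-difference analysis only the part due to differing change over the year would remain.

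**What to change.** Rewrite the day-1 paragraph to agree with Eligibility criteria, Recruitment and the allocation section, with one order for both arms:

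1. the same neutral information to all eligible families;
2. written consent and Unique ID;
3. baseline assessment;
4. opening of the next envelope;
5. only then, sensitisation of intervention parents.

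State that every consented child is analysed in the allocated arm from envelope opening, including children whose families then refuse sessions.

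Rewriting cannot change steps already taken. Trial status gives a recruitment start of January 2023, and Recruitment planned entry for January to March 2023. The sponsor should therefore also state when envelopes were actually opened relative to consent. It should report, by arm, how many families were randomised before consent and how many of those then refused. These counts would help a reader judge whether selective entry could have occurred.

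The cost is one paragraph of text and a count from the enrolment records, with no added procedure for families. The drawback is that some families who decline sessions stay in the analysis and slightly dilute the estimated effect.

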### Recruitment

Parents of children reporting to A.V.B.R.H. in the first three months (January-March 2023) will be enrolled in the trial. All participants consenting to participate in the study will be assigned the Unique ID. Using a blocked randomization process with age groups as the Blocking variable, participants will be allocated to intervention or control groups. Age groups will be:
1.Six months to 30 months2.31 months to 60 months.

All children hospitalized in A.V.B.R.H., scheduled to stay for a minimum of three days in the hospital, and their parents signed the informed consent will be enrolled in the study.

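### The first-day text places randomisation and a briefing of intervention parents before written consent, contrary to the consent-first order in three other sections; if it was followed, parents consented knowing their arm.

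*Protocol article*

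**What the plan says.** Criteria for group sessions at the hospital sets out intervention delivery day by day. For the first day, after contact with families on the ward, it says "Randomization will be done and the parents in intervention arm will be sensitized about Play Therapy Programme". The next sentence begins "Written informed consents of parents will be taken from those who consent for participation and will be enrolled in the programme" and goes on to include the e-learning platform and WhatsApp group in that enrolment.

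Three other sections give a different order:

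- Eligibility criteria: "The children and their parents signing the informed consent will be enrolled in the study". Enrolled children then receive a Unique ID, and after that "Children will be allocated to intervention or control groups using a block randomization process".
- Recruitment: "All participants consenting to participate in the study will be assigned the Unique ID", followed by "Using a blocked randomization process with age groups as the Blocking variable, participants will be allocated to intervention or control groups".
- Assignment of interventions: allocation again gives the ID to those who consent and then allocates them. It adds that "trained assistants will enroll the participants, and assign participants to intervention and control groups" and that "Sequentially numbered, opaque, sealed envelopes will be used for implementing the allocation sequence".

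**The concern.** Concealed allocation prevents selection only if the decision to take part is final before the envelope is opened. As the first-day text is written, there is already an identified intervention arm, and its parents have already been briefed, when consent is first mentioned. The control group, by the protocol's own account, receives no messages about the intervention.

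The two arms are offered very different things. One receives daily sessions in hospital and a year of home visits; the other receives assessments and follow-up contacts. A parent who knows the arm may accept or decline because of it. If families who decline at that point are not counted, the groups compared are selected by willingness given the arm as well as by chance. Willingness is plausibly related to home circumstances, and so to child development. Block balance within age groups does not correct this, and an intention-to-treat analysis helps only if it includes the families who declined.

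**Working it through.** **1. The plan's own figure.** Sample size gives d = 0.5, SD = 1.69, two-sided 5% and 80% power. n = 2 × (1.96 + 0.84)² × 1.69² / 0.5² = 2 × 7.84 × 2.8561 / 0.25 = 179.1, so 180 per arm. The stated figure reproduces (power at 180 per arm is 80.1%), and the point here does not depend on it.

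**2. The orders side by side.**

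- First-day text: ward contact; randomisation; briefing of intervention parents; written consent from those willing; enrolment.
- Eligibility criteria: consent and enrolment; Unique ID; allocation.
- Recruitment: consent; Unique ID; allocation.
- Allocation section: consent; Unique ID; allocation, with assistants enrolling and then assigning.

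The last three agree with each other, and the first conflicts with all of them. No section says what happens to a child who has been randomised and whose parents then decline.

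**3. What follows under each order.** Under consent first, a family that declines was never randomised, and this source of bias is absent. Under the first-day order, a family can be randomised, learn its arm and then decline. Bias then needs two further conditions: that declining depends on the arm, and that those who decline are left out of the analysis.

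**4. Illustration of size.** The documents give no refusal rates, so every refusal input below is an assumption. Both models use an unadjusted endline comparison with no true effect. The rejection rate is 1 − Φ(1.96 − b/SE) + Φ(−1.96 − b/SE), where b is the bias in points.

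*Model A: 180 per arm counted after refusals.* Assume 5% decline in either case, and a further share f accept only if allocated to therapy and differ from the rest by D SD. The intervention group is then 0.95 of those approached, of whom f differ by D, and the control group contains none of them. Bias = D × f / 0.95. SE = 1.69 × √(2/180) = 0.178.

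| f | D | Bias (SD) | Bias (points) | Rejection rate |
|---|---|---|---|---|
| 0.10 | 0.3 | 0.032 | 0.053 | 6.0% |
| 0.10 | 0.5 | 0.053 | 0.089 | 7.9% |
| 0.15 | 0.5 | 0.079 | 0.133 | 11.6% |
| 0.25 | 0.5 | 0.132 | 0.222 | 23.9% |

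Against a target of 0.5 points this is 0.053/0.5 = 11% to 0.222/0.5 = 44%. Sample size also words the target as 0.5 SD; on that reading it is 0.032/0.5 = 6% to 0.132/0.5 = 26%.

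*Model B: 180 randomised per arm, a share r of the intervention arm declines and is dropped.* If decliners would have scored g SD lower, the mean of those who stay, m, satisfies (1 − r)m + r(m − g) = 0, so m = r × g. For r = 5% to 30% and g = 0.25 to 0.5, the shift is 0.0125 to 0.15 SD, or 0.02 to 0.25 points. With SE = 1.69 × √(1/(180(1 − r)) + 1/180), the rejection rate is 5.2% to 25%. At r = 10% and g = 0.5 it is 7.5%.

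The bias can go in either direction, depending on which families decline.

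**5. Effect of the planned analyses.** Statistical methods also plans adjusted and difference-in-difference analyses of the development scores. Difference-in-difference removes the part of D or g that is already present at baseline and stays constant. A difference in how the children develop over the year remains. The figures in step 4 therefore apply to the unadjusted endline test only.

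**The case against.** The strongest reply is that the first-day paragraph is loose narration. It is introduced as a description of intervention delivery, no connecting word places consent after randomisation, and the three sections that deal with eligibility, recruitment and allocation agree on consent first. The enrolment it mentions is into the programme and its messaging group, so it may describe how intervention families are brought into the sessions after trial consent. It does not say when or how control parents are asked. Figures 1 and 2, which may bear on the order and on how refusals are counted, are not available here.

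Much of this stands. A drafting slip is possible, and the documents cannot rule it out. But the paragraph names an intervention arm before it mentions consent, and it is the day-by-day account that assistants could be expected to follow. Even read as programme onboarding, it gives intervention families a decision after allocation, and nothing states that those who decline then remain in the analysis.

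Two stronger readings are tempting. A reader might infer that the arms analysed are no longer the arms randomised. That would require the first-day order to have been used, refusal to depend on the arm, and decliners to have been excluded; the documents establish none of these. A reader might also infer that decliners left no record. No section says so, and sequentially numbered envelopes may make them traceable.

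It is also fair to say that changing the procedure comes late: the version is dated October 2024, the stated recruitment window was January to March 2023, and completion was expected in May 2024.

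**Conclusion.** The contradiction is real and lies in the current text. The first-day paragraph and the three other sections cannot both describe what was done, and they differ on the step that makes the comparison a randomised one. The bias is conditional: it arises only if the first-day order was used and families who declined after allocation were left out. Its size cannot be derived from the documents. The illustrative range, about 0.01 to 0.15 SD with rejection rates from 5% to 25%, rests wholly on assumed refusal rates and an unadjusted endline test. A reader might take its upper end as the trial's error rate; the documents do not support that. The point is still more than clerical, because the answer decides whether the result can be read as free of selection after allocation.

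**What to change.** 1. Rewrite the first-day paragraph to agree with Eligibility criteria, Recruitment and the allocation section: the same neutral information to all eligible parents, signed consent, Unique ID, envelope opened, and only then the briefing of intervention parents. If the consent sentence was meant as onboarding to the programme, say so and separate it from trial consent.
2. State that every child whose envelope was opened is counted and analysed in the allocated arm, including those whose families later decline the sessions.
3. Because enrolment is probably over, state which order was actually used. If any child was randomised before consent, report refusals after allocation by arm and limit the conclusions accordingly. Comparing the numbered envelopes opened with the Unique IDs issued may supply that count.
4. Label any bias or rejection-rate figures as illustrations on assumed refusal rates for an unadjusted endline test.

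The cost is a few sentences of text and a check of the allocation records; no extra patients, visits or staff are needed. One small drawback of consent first is that parents who leave on learning that they are controls appear as withdrawals after randomisation, but they are then visible and can be counted. Re-ordering the text cannot change who has already been enrolled, so item 3 matters most for interpretation.
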